## Abstract

**Background:**

Due to shorter hospitalization, patients have to take responsibility for their rehabilitation period at a very early stage. The objective of this trial is to study the effects of two treatment schemes following total knee arthroplasty: conventional treatment following discharge from hospital and early follow-up by telephone consultations in addition to conventional treatment following discharge from hospital. The ultimate aim is to increase the effectiveness of the treatment by improving patients' health status, promote self-efficacy, and reduce the number of acute visits to the orthopaedic outpatient clinic during the rehabilitation period.

**Method/design:**

The design is a randomized un-blinded parallel group clinical trial conducted at the Department of Orthopaedic Surgery, Gentofte Hospital, the Capital Region of Denmark. In total, 116 patients will be allocated by an external randomization program to 2 groups: an intervention group following usual treatment after discharge supplemented by a nurse managed structured follow-up consultation conducted by telephone 4 and 14 days after discharge from hospital and a control group following treatment as usual. The consultations are structured by key subjects relevant to assess the health status according to the VIPS-model (the Swedish acronym for the concepts Well-being, Integrity, Prevention and Safety). The content of the consultations can vary according to the patients´ individual situations and needs. All consultations are conducted by the researcher responsible for the trial.

The effect is measured 1, 3, 6 and 12 months post-surgery. The primary outcome is self-reported physical function measured by The Western Ontario and McMaster Universities Arthritis Index. Secondary outcomes are self-reported health-related quality of life, general self-efficacy and the number of acute visits to the orthopaedic outpatient clinic.

**Discussion:**

The result of this trial is expected to provide new knowledge to support the development of targeted and effective follow-up after total knee arthroplasty in order to improve the patients´ health-related knowledge and skills of being able to take actively part in their illness and improve their health status.

**Trial registration:**

ClinicalTrials.gov: NCT01771315

## Background

### Introduction

The number of primary total knee arthroplasty (TKA) procedures is increasing and estimated to 1.4 million worldwide in 2015 [1]. In Denmark approximately 9000 TKA procedures are performed annually [2]. The main clinical indication for TKA is osteoarthritis [3] causing severe pain and substantial functional disabilities, leading to a decrease in health-related quality of life [4].

TKA is a common procedure that, despite of low level of mortality and complications, entails a severe surgical trauma and a protracted recovery [5].

The implementation of the fast-track programs for surgical patients has reduced the stay in hospital for TKA-patients, and the length of stay is now only around 3 days in several Danish surgical centres [6]. Commonly the patients are discharged to home and referred to physiotherapy in the community settings, with only one scheduled follow-up by the surgeon 3 months post-surgery.

During the early rehabilitation period TKA- patients have experienced several health problems especially physical ones [7]. In a survey conducted at Gentofte University Hospital in 2011, 96% out of 86 patients identified 1–7 physical postoperative health problems two to three weeks after undergoing TKA (unpublished observations by the researcher responsible for this trial). The health-related information given during the admission course has been difficult to transfer to the home settings [8], and following discharge the patients have needed further guidance [9]. Although the problems were apparent, the patients were reluctant to contact health professionals due to a belief that their problems were too insignificant to bother health care providers with [10]. During the rehabilitation period the experience of inadequate preparation for physical symptoms and psychological reactions, as well as unrealistic expectations to activity level have led to anxiety, depression and disappointment [11] to the extent of affecting the patients´ general health [12].

Self-efficacy is the degree of belief of having adequate action-oriented resources to control events affecting the everyday life successfully [13]. Self-efficacy is positively correlated with physical and mental aspects of health [14]. Self-efficacy is an important parameter during the rehabilitation period following TKA [15-17] by influencing physical function and mental health [16].

### Rationale for the study

Follow-up interventions after discharge of TKA patients have especially focused on the effect of various programs for physiotherapy. Internet based as well as home-based physiotherapy was assessed to be as effective as outpatient physiotherapy measured by physical function and health-related quality of life, respectively [18-21]. An intensive outpatient physiotherapy program additional to standard care (home-based exercise program) improved physical functional ability and health related quality of life compared to standard care [22]. Postoperative exercise is a highly prioritized part of the TKA treatment, aiming at improving the ability to practice daily activities immediately after surgery as well as maximizing the long term functional benefit of TKA [23]. However, the early rehabilitation period after TKA is characterized by a broad range of physical as well as mental symptoms as mentioned in the introduction.

A standardized follow-up program involving an exit video with role models, extra information through newsletters about the rehabilitation process, two telephone calls and weekly telephone hours was evaluated in a randomized clinical trial. The trial included 103 patients undergoing total knee and total hip arthroplasty eligible for a short stay (less than 6 days) in hospital and showed no effect on self-efficacy, social support and pain coping [24]. The program was not designed to provide individual counselling according to the patients´ personal circumstances and the progress during their rehabilitation period. In contrast a structured telephone follow-up focusing on individual care in regard to physical, social and mental aspects of the rehabilitation period had a positive effect on physical function, as well as general and mental health in 122 patients aged 65 years or older undergoing total hip arthroplasty [25]. It is assumed that it is possible to retrieve a corresponding positive effect for patients undergoing TKA.

### Aim

The aim of this trial is to evaluate the effect of a structured nurse managed telephone follow-up in the early rehabilitation period, based on the patient´s individual situation related to physical as well as psychosocial problems following TKA.

We hypothesize that telephone follow-up as a supplement to conventional treatment will improve health status and self-efficacy and reduce the number of acute clinical outpatient consultations after TKA compared to conventional treatment.

## Method/Design

The study is designed as a randomized single centre parallel group clinical trial. The participants are allocated to two groups: an intervention group receiving telephone follow-up as supplement to conventional treatment and a control group that follows conventional treatment (see Figure 1).

**Figure 1 F1:**
[figure not shown]
Flow-chart for the trial.

### Primary outcome

In a 12 months period the effect of telephone follow-up is primarily assessed by a significant improvement of ≥ 12 points for the physical function score in the intervention group compared to the control group measured by the disease-specific Western Ontario and McMaster Universities Osteoarthritis (WOMAC) LK 3.1 Index [26].

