### Sample size

Calculation of the sample size is based on the primary outcome physical function in the WOMAC Index based on the smallest clinically relevant improvement, which is reported to 5.3, 11.8 and 20.4 points related to low, intermediate and high baseline score tertiles respectively [42]. A difference of a minimum of 12 points in favour of the intervention group compared to the control group during a period of 12 months post-surgery is assessed as a clinical relevant outcome in this trial and determined as basis for estimation of the sample size. The standard deviation for the entire population is estimated to 18 points. Sample size is calculated with the assumption of normally distributed data with α = 5% and 1-β = 90% and an equal number of patients in each group. It is estimated that 48 patients are needed in each group. With an expected drop out rate of 20% 58 patients have to be included in each group.

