### Outcome analysis

Data will be entered in EpiData version 3.1. The statistical software STATA will be used for data analysis. Ratio-scaled data from both groups (intervention and control) will be compared by using parametric methods if data are normally distributed, and if not, nonparametric methods will be used. Nominal scale data will be compared by Chi-square test or by a 95% confidence interval when comparative measures. Categorical variables will be compared using the Pearson´s chi-square test and the Mann–Whitney test, and two-sided level of significance p < 0.05, if it is found optimal. For continuous data changes within the groups will be analysed by using a paired t-test. P < 0.05 will be considered as being statistically significant. Due to the repeated measures a logistic regression analysis will be performed.

All patients will be analysed in the groups to which they are randomly allocated according to intention to treat analysis. This analysis is primarily based on imputation of outcomes by carrying the last known outcome status forward and is supplemented by sensitivity analysis to examine the effect on the results.

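### The primary outcome is worded as a significant difference of at least 12 points, but the 90% power belongs to a test of zero difference; applied literally, the wording would be met only about half the time if the true difference is 12

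*Protocol article*

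**What the plan says.** Under Primary outcome, the article assesses the effect over a 12-month period by "a significant improvement of ≥ 12 points for the physical function score in the intervention group compared to the control group". This is its only full statement of the primary criterion. The Abstract names self-reported physical function on the WOMAC as primary and gives no threshold.

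Under Sample size, the same 12 points return in a second role. "A difference of a minimum of 12 points in favour of the intervention group compared to the control group during a period of 12 months" after surgery is judged clinically relevant and is "determined as basis for estimation of the sample size". The other inputs are "The standard deviation for the entire population is estimated to 18 points" and a calculation "with α = 5% and 1-β = 90% and an equal number of patients in each group". The result is 48 per group, raised to 58 for drop-out.

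Under Outcome analysis, the rule is p < 0.05, with a "two-sided level of significance p < 0.05" named in the sentence on categorical variables. That section makes no use of 12 points.

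**The concern.** The number 12 appears to do two jobs: it is the true effect assumed in planning, and it is a bar that the result must clear. A trial sized for 90% power to show a difference from zero does not have a 90% chance of producing an estimate at or above the assumed true effect. An unbiased estimate falls below its own target about half the time.

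What is at stake is how a middling result is read. With an observed difference of 9 points and p < 0.05, one reader could call the trial positive from the Outcome analysis section, and another could call it not met from the Primary outcome section. The trial is un-blinded and its primary outcome is self-reported, so that choice should not be left open until the data are known.

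**Working it through.** **Inputs**
- Difference 12 points, SD 18, α = 5%, power 90%, 48 evaluable per group, 58 enrolled per group: Sample size section.
- 1:1 allocation: Randomization and blinding section.
- Two-sided test: named in the Outcome analysis section for categorical variables. The Sample size section does not give the sidedness, so it is checked in step 1.
- Differences are signed so that positive favours the intervention (on this scale a lower WOMAC score is better).
- One comparison of two means at a single time is assumed, as in the plan's own calculation.

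**Step 1. Reproduce the plan's figure.**
n per group = 2 × [18 × (1.960 + 1.2816) / 12]² = 47.28, rounded up to 48. This matches. A one-sided 5% test would give 39, so the plan's calculation is two-sided.

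**Step 2. What the 90% refers to.**
SE of the difference = 18 × √(2/48) = 3.67 points.
Power to reject zero at a true difference of 12 = Φ(12/3.67 − 1.96) = 0.904 by the normal approximation, or 0.898 by the exact t-test. The stated 90% is therefore right for the test of zero difference.

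**Step 3. The smallest significant observed difference.**
Normal: 1.96 × 3.67 = 7.2 points. With the t distribution on 94 degrees of freedom: 7.3 points.

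**Step 4. The literal criterion, p < 0.05 and observed difference ≥ 12.**
Because 12 is well above 7.3, practically every estimate of 12 or more is already significant, and the 12-point condition alone decides.
P(estimate ≥ 12 | true difference δ) = 1 − Φ((12 − δ)/3.67):

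| True difference δ | Chance of meeting the literal criterion |
|---|---|
| 10 | 29% |
| 12 | 50% |
| 14 | 71% |
| 16.7 | 90% |

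The last row comes from 12 + 1.2816 × 3.67 = 16.7. A simulation at n = 48 with the SD estimated from the data gave 49.9% at δ = 12.

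**Step 5. The gap between the two rules.**
At a true difference of 12, about 0.90 − 0.50 = 0.40 of trials would be significant and yet show less than 12 points.

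**Step 6. Does the number analysed matter?**

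| n per group | SE | Smallest significant difference (normal) | P(estimate ≥ 12) at δ = 12 | δ needed for 90% |
|---|---|---|---|---|
| 46 | 3.75 | 7.4 | 50% | 16.8 |
| 48 | 3.67 | 7.2 | 50% | 16.7 |
| 58 | 3.34 | 6.6 | 50% | 16.3 |

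The 50% does not move, because the bar sits exactly at the assumed truth. More patients narrow the spread around 12 but do not shift its centre.

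**The case against.** The best defence is that 12 is only the planning difference. The Sample size section calls it clinically relevant and uses it to set n. The WOMAC section calls it the hypothesised improvement, and the Discussion refers to it as the stated relevant difference between groups. The Abstract defines the primary outcome without a threshold, and the Outcome analysis section tests at p < 0.05 alone. On that reading the 90% is the power of the test that will be run, and nothing is wrong with the sample size.

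Much of this stands. It makes the 50% conditional on the literal reading. It does not clear the Primary outcome sentence, which then states a rule that the trial does not intend to use.

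Three stronger readings are tempting, and the article does not support them:
- *The power is really 50%, or a significant benefit of 8 to 11 points will be called a failure.* The article never says how such a result would be reported and does not use the language of success or failure. It leaves the matter open.
- *The criterion means significantly more than 12, with a chance of only 2.5% at a true difference of 12.* Nothing describes a test against a margin of 12 or a confidence limit compared with 12.
- *The 12 points is the wrong kind of quantity.* The cited values are "reported to 5.3, 11.8 and 20.4 points related to low, intermediate and high baseline score tertiles respectively", and a reader might infer that they are changes within patients and not differences between arms. That depends on a source not at hand, and the authors make their own judgement that 12 is relevant between groups. Likewise, 12 points against the expected 6-month mean of 32 is a 37.5% reduction (12/32). This is ambitious but not an error, and the article itself notes that a mean of 32 leaves room for it.

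It is also fair that the 7.3-point cut-off depends on the number analysed. With all 58 per group included, as intention to treat with imputation would allow, it falls to about 6.6.

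**Conclusion.** The concern holds as a mismatch in wording between the Primary outcome section and the Sample size and Outcome analysis sections. Either the primary outcome sentence is literal, and the stated 90% does not belong to it (about 50% at a true difference of 12), or 12 is only the planning difference, and the sentence misstates the criterion. On both readings one passage has to change.

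The range left ambiguous runs from about 7.3 to just under 12 observed points, given SD 18, 48 analysed per group and a single two-sample comparison. The 50% needs only an unbiased, roughly symmetric estimate and a significance cut-off well below 12. It does not depend on the sample size within the plan's range.

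This is not a fault in the sample size, which reproduces, and it does not show that the trial is underpowered for the test in the Outcome analysis section. It is a cheap correction that matters for interpretation, and it should be made before results are known.

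**What to change.** Reword the Primary outcome section so that the primary outcome is the between-group mean difference in WOMAC physical function, and a positive result is two-sided p < 0.05 (95% confidence interval excluding zero) in favour of the intervention. Keep 12 points as the planning difference under Sample size, and as a reference against which the estimate and its confidence interval are interpreted.

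If the sponsor does intend 12 points as a success criterion, say so in the Outcome analysis section as well, and restate the power for that rule: about 50% at a true difference of 12, with about 16.7 points needed for 90% at 48 per group.

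The cost of the first option is one sentence. The sample size, test and data collection stay as they are.

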### Secondary outcomes

Secondary analysis will assess the effect of telephone follow-up in the intervention group compared to the control group by change in pain and stiffness scores in WOMAC LK 3.1 Index, change in health-related quality of life measured by the Medical Outcomes Study Short Form (SF-36) [27], change in the General Self-Efficacy Scale score [28], and the number of acute visits to the orthopaedic outpatient clinic.

### Trial population and patient recruitment

All patients are recruited from Orthopaedic Department, Gentofte University Hospital – a medium sized hospital in the Capital Region of Denmark which performs approximately 600 primary TKA per year.

Patients who meet the inclusion criteria, and none of the exclusion criteria (see Table 1), are consecutively enrolled in the trial during admission. The researcher screens daily for eligibility of all patients scheduled for elective primary TKA. First day post-surgery potential participants are informed verbally and in writing about the aim and course of the trial with neutral use of words. The information is given by research assistants not involved in the trial and in their absence by the researcher.

**Table 1 T1:** Eligibility criteria

**Inclusion criteria**	**Exclusion criteria**
● Primary first-time total knee arthroplasty due to osteoarthritis	● In terminal phase of another serious illness such as e.g. cancer with expected lifetime less than 6 months
● Age > 18 years	● Previous total hip arthroplasty
● Followed conventional course and discharged ≤ 4 days after surgery	
● Understand and talk Danish	
● Signed informed consent before randomization	

### Ethics

The Regional Committee on Health Research Ethics has assessed the trial and an approval is not required to initiate this trial. The regional Danish Protection Agency has approved the trial (no. 01839 GEH-2012-033).

The trial is conducted according to the latest Declaration of Helsinki [29]. All eligible patients are informed verbally and in writing about the aim and practical carrying out of the trial besides their rights as participants. All participants sign written informed consent forms prior to randomization.

All data will be handled with confidentiality, and the patients are ensured anonymity.

The trial is registered on CilinicalTrials.gov (NCT 01771315).

### Randomization and blinding

Patients are randomized 1:1 to the intervention group or the control group respectively. The randomization is performed centrally by a web-based randomization program and in blocks unknown to the investigator and other subjects involved in the study. The randomization is executed just before discharge of the patients from hospital.

### Conventional treatment

The patients are admitted to the orthopaedic department on the day of surgery or the evening before. Discharge is scheduled 2–3 days post-surgery based on the following criteria: able to manage personal hygiene by themselves, to walk with one or two crutches, and to climb stairs. The patients are referred to physiotherapy in the community settings, to removal of stitches or stables by their general practitioner, and to an outpatient consultation by the surgeon 3 months post-surgery.

All participants follow the conventional course of treatment for TKA-patients including the program for patient education pre-surgery conducted by a surgeon, physiotherapist, occupational therapist and a nurse, focusing on the surgical intervention, possible complications and risks, the admission course, and introduction to physical exercise training and equipment.

### Intervention

The participants allocated to the intervention group receive telephone follow-up 4 and 14 days post discharge in addition to conventional treatment. A uniform structure of the consultations is based on key subjects for nursing status defined by the VIPS-model (the Swedish acronym for the concepts Well-being, Integrity, Prevention and Safety). The VIPS-model is a process-oriented documentation model developed to generate structured general information about the patient’s condition, needs, desires, problems and resources relevant for nursing to provide adequate nursing interventions and evaluation of the outcomes [30,31]. The nursing status is based on predefined key subjects identified as relevant to assess the health status in the course of disease [31]. The telephone follow-up consultations are structured and contain the following key subjects: communication, cognition/development, breathing/circulation, nutrition, elimination, sleep, pain/perception, skin/tissue, sexuality/reproduction, activity and psychosocial /spirituality/culture. The themes are supplemented with specific issues relevant to health status after TKA in regard to treatment and observation of the wound and the operated limb, management of painkillers, and ability to exercise as recommended. However, the course of the consultations may vary due to the individual needs of the patients.

All interventions are conducted by the researcher responsible for this trial. The adherence of the protocol for the intervention is assessed by audiotaping consultations executed the first Wednesday in each month. Subsequently the records are checked by an external research assistant to ensure compliance with the protocol.

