All interventions in this trial are conducted by the first author, reflecting the practice of that specific nurse and representing a positive attitude to the intervention, which could influence the outcome positively. The performance of the intervention will not reflect the intervention in an everyday clinical practice, which is influenced by the skills and attitudes of a range of nurses and the intervention needs to be tested in every day nursing practice to enhance generalizability. Random checks by audiotaping the intervention sessions and documentation in case report forms, assess treatment adherence essential to be able to appraise the feasibility and reproducibility of the intervention in clinical practice [51].

The effect of follow-up consultations by telephone after TKA has not previously been studied. Patient satisfaction with care related to information and contact with health professionals during stay in hospital was positively correlated with self-perceived health status up to 12 months after total hip and knee arthroplasty [52,53], and a long term effect of telephone follow-up consultations after TKA cannot be excluded. Due to timing and content of the intervention the effect is expected to be strongest and with the stated clinical relevant difference in scores between groups in the early recovery period.

Selection of patients enrolled in a trial may lead to problems with generalizability if the selected population differs in important ways to the more general one [44]. The practical value of a trial is supported by enrolling patients with characteristics that reflect the range and distribution of patients observed in clinical practice for a particular problem [54]. To enhance generalizability, all patients admitted are consecutively enrolled in this trial if they meet the inclusion criteria and none of the exclusion criteria. However, the sample in this trial will only represent the group of patients with a short stay in hospital, which minimizes the time for health-related counselling and information, but also increases the possibility of a positive outcome of the study.

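### Adherence checks are called random, but recording falls on one fixed day each month that the only caller knows in advance, so the adherence and reproducibility statement can be too favourable

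*Protocol article*

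**What the plan says.** The Intervention section of the protocol article sets out the fidelity check. Intervention patients "receive telephone follow-up 4 and 14 days post discharge in addition to conventional treatment". On who calls: "All interventions are conducted by the researcher responsible for this trial". Adherence is assessed by "audiotaping consultations executed the first Wednesday in each month", and then: "Subsequently the records are checked by an external research assistant to ensure compliance with the protocol".

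The Discussion describes the same monitoring differently: "Random checks by audiotaping the intervention sessions and documentation in case report forms, assess treatment adherence". It adds that this assessment is essential for judging how feasible and repeatable the intervention would be in practice. It also identifies the caller ("All interventions in this trial are conducted by the first author") and acknowledges that person's stance as "representing a positive attitude to the intervention, which could influence the outcome positively".

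The Data collection section lists further records from the calls: their length, the health problems found and the counselling given under each preset theme. Nowhere does the article describe a random draw of days or calls, or any step that keeps the recording days from the caller.

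**The concern.** A random check protects against one specific problem: the person being checked cannot tell which sessions will be examined, so the examined sessions stand for the rest. A fixed monthly date gives no such protection when that person knows the date. The caller can prepare more carefully, or keep closer to the structure, on recording days without intending to distort anything.

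This matters more than usual here for two reasons. The consultation content may vary with the patient's needs, so delivery can drift from the structure. And a single caller gives every consultation, so no comparison between callers could reveal drift. What is at stake is the statement on adherence and reproducibility: a reader deciding whether the programme was delivered as described, and whether others could deliver it, would give a random audit more weight than this one can bear.

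**Working it through.** **The two descriptions side by side**

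| Feature | Intervention section | Discussion |
|---|---|---|
| Selection of recorded calls | Calendar rule, one set day a month | Described as random |
| Caller | The responsible researcher, for all calls | The first author, for all calls |
| Who checks the recordings | External research assistant | Not stated |
| Other adherence source | Not stated | Case report forms |

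The selection rule and its label do not agree. That the caller knows the days is an inference, because the article does not discuss it. It is a firm one: the rule is a fixed date printed in the protocol, and the caller is that protocol's first author.

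**How many calls the rule would catch**

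The plan gives no number of recordings, so there is no stated figure to reproduce. The count below is an estimate.

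Inputs:
- Patients in the intervention group: 58 (Sample size). The plan's own step is 48 × 1.20 = 57.6, rounded up to 58.
- Calls per patient: 2 (Intervention).
- Period: January 2013 to the end of 2013, about 12 months (Results), hence 12 first Wednesdays.
- Assumption, not in the documents: calls are spread evenly over the days on which calls are made.

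Planned calls: 58 × 2 = 116.

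Expected recorded calls = calls × 12 / calling days in the year:
- calls on all seven days: 116 × 12 / 365 = 3.8, or 3.3% of calls;
- calls on working days only (261 in the year): 116 × 12 / 261 = 5.3, or 4.6% of calls.

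If only the 48 patients per group left after the expected drop-out received both calls, there would be 48 × 2 = 96 calls. The count would then be 96 × 12 / 365 = 3.2 to 96 × 12 / 261 = 4.4.

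**Limit of the even-spread assumption**

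If the call days are kept exactly, a Wednesday call on day 4 comes only from a Saturday discharge (Saturday + 4 days). A Wednesday call on day 14 comes only from a Wednesday discharge (14 days = two full weeks). The true count could then differ from 4 to 5, and the recorded calls would also be selected by day of discharge.

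**What cannot be computed**

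The document has no data on adherence on recorded or unrecorded days, so neither the occurrence nor the size of a bias can be derived.

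**The case against.** The strongest reply is that this is mainly a matter of wording. Random may be meant loosely, as in a spot check, and a systematic calendar sample is a legitimate choice. Call dates follow from discharge dates, so the caller has little freedom to choose which patients fall on a recording day. An external person checks the recordings. The Discussion already discloses the single caller, that person's attitude and the need to test the intervention in everyday nursing.

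Much of this stands. The external check limits bias in rating, and the fixed call times limit selection of patients. Neither stops the caller from behaving differently on a known recording day. Disclosing the caller's attitude does not disclose that the audit is foreseeable.

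A reader might also infer more than the documents support:
- *That the recordings are the only evidence of delivery.* They are not. The Discussion names case report forms in the same sentence, and Data collection describes theme-level records of the calls. What can be said is that no independent completion or check of those records is described, whereas it is for the recordings.
- *That the trial's result depends on the audit.* It does not. The primary outcome is compared between the groups as randomised, and the article describes no analysis that uses the audit. Only the interpretation of what was delivered is touched.
- *That the small sample measures the flaw.* With 5 audited calls and no deviation, the exact two-sided 95% upper limit for the deviation rate is 1 − 0.025^(1/5) = 52%. Five calls drawn at random would give the same limit, so it says nothing about foreseeability. Nor does the article say that it will estimate a deviation rate.
- *That the caller did behave differently.* Nothing in the document shows this.

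**Conclusion.** The point holds in a limited form. The Discussion calls random what the Intervention section fixes by calendar, and the only caller can foresee every recording day. Audited calls need not represent the others, so the statement on adherence and reproducibility can be too favourable. It is not shown that it will be, or by how much.

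The audit would cover roughly 4 to 5 of 116 planned calls. This rests on full recruitment, both calls made to every intervention patient, 12 months of calling and an even spread of calls over days. The conclusion about foreseeability does not depend on that count. The randomised primary comparison and the sample size are untouched. The change is worth making because it is cheap and protects an assessment that the protocol itself treats as essential.

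**What to change.** 1. For the remaining calls, record every consultation, with the patient's consent. About half the participants were enrolled when the article was written, so a substantial share of calls can still be covered.
2. Have the external research assistant, not the caller, draw the calls to be checked at random after they have taken place. The draw should cover both day-4 and day-14 calls. The number checked can stay as it is.
3. Bring the Intervention section and the Discussion into line with this rule.
4. For calls already audited under the calendar rule, drop the word random, report how many were audited, and state as a limitation that the caller knew the recording days.

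Cost: consent to, and storage of, more recordings. Recording and an external checker are already in place, so no extra staff are needed and the checking workload is unchanged. The gain is partial, because calls made before the change remain covered only by the calendar rule.
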